## Abstract

**ᅟ:**

The overall purpose of this study is to provide proof of concept for introducing the anthracycline epirubicin as an effective, biomarker-guided treatment for metastatic colorectal cancer (mCRC) patients who are refractory to treatment with oxaliplatin-based chemotherapy and have *TOP2A* gene amplification in their tumor cells.

**Background:**

Epirubicin is an anthracycline that targets DNA topoisomerase 2-α enzyme encoded by the *TOP2A* gene. It is used for treatment of several malignancies, but currently not in CRC. *TOP2A* gene amplifications predict improved efficacy of epirubicin in patients with breast cancer and thus could be an alternative option for patients with CRC and amplified *TOP2A* gene. We have previously analysed the frequency of *TOP2A* gene aberrations in CRC and found that 46.6 % of these tumors had *TOP2A* copy gain and 2.0 % had loss of *TOP2A* when compared to adjacent normal tissue. The *TOP2A* gene is located on chromosome 17 and when the *TOP2A*/CEN-17 ratio was applied to identify tumors with gene loss or amplifications, 10.5 % had a ratio ≥ 1.5 consistent with gene amplification and 2.6 % had a ratio ≤ 0.8 suggesting gene deletions. Based on these observations and the knowledge gained from treatment of breast cancer patients, we have initiated a prospective clinical, phase II protocol using epirubicin (90 mg/m2 iv q 3 weeks) in mCRC patients, who are refractory to treatment with oxaliplatin.

**Methods/Design:**

The study is an open label, single arm, phase II study, investigating the efficacy of epirubicin in patients with oxaliplatin refractory mCRC and with a cancer cell *TOP2A*/CEN-17 ratio ≥ 1.5. *TOP2A* gene amplification measured by fluorescence in situ hybridization. A total of 25 evaluable patients (15 + 10 in two steps) will be included (Simon’s two-stage minimax design). Every nine weeks, response is measured by computed tomography imaging and evaluated according to RECIST 1.1. The primary end-point of the study is progression-free survival.

**Trial registration:**

Eudract no. 2013-001648-79.

## Background

Colorectal cancer (CRC) is a major health problem since it is among the five most prevalent cancers [1, 2]. Over the last decade, the use of novel treatment modalities and complex treatment strategies in terms of optimized surgery, adjuvant chemotherapy, and novel targeted biological agents have contributed to significant improvement of outcome of the entire population of patients with CRC. However, only three cytotoxic drugs (fluorouracil (5-FU), oxaliplatin and irinotecan) are recommended as standard treatment in patients with metastatic CRC (mCRC). In Europe, the routine clinical management of patients with primary CRC involves adjuvant treatment with 5-FU/Leucovorin (LV) and oxaliplatin (FOLFOX, FLOX or XELOX) given to high-risk patients [3–6]. In the treatment of mCRC, patients who have yet not received oxaliplatin will often be offered FOLFOX, FLOX or XELOX, followed by 5-FU/LV and irinotecan (FOLFIRI, FLIRI or XELIRI) at progression, or vice versa [7–10]. Chemotherapy may be combined with the EGF-receptor targeting antibodies cetuximab or panitumumab in patients with *RAS* wild type tumors [11–14], while patients with *RAS* mutated tumors often will receive the VEGF targeting antibody bevacizumab [15, 16]. The objective response rate to first-line systemic treatment of mCRC patients approximates 50 % [10, 17]. However, only 10 % of mCRC patients will obtain objective response during second-line treatment [10], suggesting that there is a high degree of cross-resistance between the used drugs. Improvements in mCRC treatment may be achieved through the development of novel drugs with new molecular mechanisms of action and thus lack of cross-resistance with currently used drugs. However, drug development is expensive (estimated cost is 1 Bill USD per drug), takes a long time (12–15 years) and the risk of failure in late stage clinical trials is extremely high. An alternative to the drug development approach is to search for novel predictive biomarkers that can guide personalized treatment and thereby select the right drug for the right patient at the right time. Using predictive biomarkers will increase the therapeutic index and avoid side effects among the many patients who will not benefit from the treatment. A third way to address these medical problems is to test whether drugs being used in some other cancer types might have beneficial effects also in CRC. However, with an expected relatively low response rate, such drugs should only be used together with companion diagnostics allowing for a pre-treatment selection of patients with the highest likelihood of obtaining benefit from the treatment. This third approach is called biomarker guided repurposing and is the foundation for the present protocol, where we investigate whether epirubicin has a beneficial effect in oxaliplatin resistant mCRC patients with *TOP2A* gene amplification.

### Epirubicin and TOP2A

The anthracycline epirubicin exerts its antitumor effects by interference with the synthesis and function of DNA and is most active in the S-phase of the cell cycle [18]. It is metabolized in the liver and primarily eliminated in the bile. The main molecular target of epirubicin is the DNA topoisomerase 2-α enzyme (Top2α) that plays a key role in maintaining the topological status of chromosomes during DNA replication and transcription. During DNA transcription, Top2α removes DNA supercoiling, and at the end of DNA replication, Top2α is essential for chromosome condensation and segregation. In this process, Top2α reversibly binds and cleaves both complementary DNA strands forming what is called a Top2 cleaving complex (Top2cc). Epirubicin leads to entrapment of Top2α in the Top2CC and thereby prevents religation of the cleaved DNA strands, which ultimately leads to DNA damage. Apart from this, epirubicin also interferes with a broad range of DNA processes through DNA intercalation [19].

*TOP2A* amplification predicts improved efficacy to epirubicin in patients with breast cancer [20, 21] and thus could be an alternative option to irinotecan-based therapy in patients with CRC and *TOP2A* amplification who relapsed on oxaliplatin containing chemotherapy. We have previously established irinotecan (SN-38, the active metabolite of irinotecan) resistant CRC cell lines, and these CRC cells were also resistant to epirubicin [22]. In contrast, our SN-38 resistant CRC cells were also resistant to epirubicin whereas our oxaliplatin resistant CRC cell lines retained sensitivity to epirubicin [[name] et al. Unpublished observations]. In another study we analysed the frequency of *TOP2A* aberrations in CRC tissue from 153 primary stage III CRC tumors and found that 46.6 % had *TOP2A* copy gain and 2.0 % *TOP2A* loss*,* when compared to adjacent normal tissue [23]. When the *TOP2A*/CEN-17 ratio was applied to identify tumors with gene loss or amplifications, 16 (10.5 %) had a ratio ≥ 1.5, consistent with gene amplification and 4 (2.6 %) had a ratio ≤ 0.8, suggesting gene deletion.

## Design/methods

### Design

The study is an open label, single arm, phase II study, investigating the efficacy of epirubicin in patients with oxaliplatin refractory mCRC and a cancer cell *TOP2A*/CEN-17 ratio ≥ 1.5. A second aim is the collection of relevant tumor and blood material for subsequent biomarker studies.

### Inclusion criteria

To be eligible for inclusion, patients must provide written informed consent. All patients must be above the age of 18 years, have WHO performance status 0–2, and a life expectancy of at least 3 months. Furthermore, patients must have histologically verified, non-resectable, oxaliplatin resistant mCRC i.e. progression during or after oxaliplatin-based therapy (at least 2 months of oxaliplatin-based palliative therapy or at least 4 months of adjuvant oxaliplatin-based therapy). Moreover, FFPE tumor tissue blocks (primary tumor biopsy/resection specimen or biopsy/resection specimen from a metastatic lesion) must be available for fluorescence *in situ* hybridization (FISH) analysis of the *TOP2A*/CEN-17 ratio and this ratio has to be ≥ 1.5.

### Treatment

Drug/dosage: Epirubicin 90 mg/m^2^ day 1 administration via fast running infusion of 0.9 % sodium chloride every 21-day. Treatment will continue until maximum cumulative dose of Epirubicin = 900 mg/m^2^, unacceptable toxicity, progressive disease at computer tomography (CT) scan according to RECIST version 1.1 or patients wish of ending treatment. Before start of treatment a baseline CT scan will be performed, and a new CT scan will be performed after every third series of epirubicin to monitor treatment response.

### Ethics

The study will be conducted in compliance with the protocol and in accordance with the ethical principles put forward in the second Declaration of Helsinki and in accordance with good clinical practice (GCP) rules. The trial was approved by the Ethics Committee of Region Syddanmark (2013-001648-79/ S-20130042) and by the Danish Medical Authority (Eudract no. 2013-001648-79).

### Study objectives

The primary end-point of the study is progression-free survival (PFS), defined as time from the first infusion of epirubicin to the first documented disease progression, according to RECIST version 1.1. Secondary end-points include overall survival (OS), response rate (RR), toxicity, and validation of tissue inhibitor of metalloproteinase-1 (TIMP-1) measured in plasma and immunohistochemically in tumor tissue, as biomarker for anthracycline sensitivity/resistance [24]. Additionally, the relationship between *TOP2A* and *TOP1* gene amplifications will be studied [25].

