### Statistics

The number of evaluable patients (the sample size) is based on Simon’s two stages Mini-max design [26]. This design ensures early study termination if there is insufficient effect. Patients will be evaluated with CT scans every 9 weeks. In randomized trials on second-line therapy, PFS is around 4 months. A tumor control rate less than 10 % after 4 months (at the time of the second evaluation CT scan) is not clinically relevant. Assuming a significance level at 0.05 (α = 0.05) and a power at 80 % (β = 0.20) it can be calculated, that 15 patients should be included in the first part of the study. The enrolment will continue until 15 patients have completed the second CT scan or experienced progressive disease. If none out of the first 15 consecutive patients achieve stable disease at the second CT scan (i.e. after 6 courses of epirubicin), we will reject our hypotheses and close the study after the first stage of accrual. If one or more patients achieve tumor control (partial response or stable disease) at the second scan, an additional 10 patients will be accrued in the second stage. If 5 out of 25 patients achieve tumor control after six courses of therapy, a tumor control rate of 30 % cannot be rejected, and it will be concluded that the treatment is effective enough to continue with future studies.

We will use non-parametric methods for calculation of patient characteristics, side effects and disease control. PFS and OS will be calculated and reported as median survival (Kaplan-Meier method).

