This study differs from the standard treatment strategy for mCRC, where the patients often will be offered irinotecan-based therapy after failure to oxaliplatin-based therapy or vice versa. Median PFS of this standard treatment is approximately 2 months, and 75 % of the patients will experience progressive disease after 4 months of treatment [10]. In the present phase II protocol with pre-selected patients, we expect that 30 % will have objective response after the first 4 months of treatment, thereby achieving an increased median PFS. All patients will be evaluated every 9 weeks, enabling a quick change in treatment strategy if a patient experiences disease progression during epirubicin treatment [32, 33]. Carefully planned and closely monitored “window of opportunity” phase II studies are feasible and ethically acceptable in mCRC patients, and may have the advantage to determine potential efficacy of novel agents without placing the patients at risk. In the present study, close monitoring of efficacy every 9 weeks will ensure that this novel treatment line with epirubicin will be offered without further delay in case of progression during epirubicin treatment, with respect to any future treatment option.

The statistical basis for the protocol is based on the fact that we expect a response rate of 30 % in this sub-population of patients with *TOP2A* aberrations, which is significantly better than the typical second line treatment these patients will be offered, which usually has response rates of 10 %. In conclusion, if the objectives of this study protocol are met, the expected 10 % of mCRC patients with a TOP2A/CEN-17 ratio ≥ 1.5 will be offered an extra line of effective treatment, which may lead to an overall improved survival in this subgroup of mCRC patients.

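### PFS is named as the primary endpoint, but sample size, alpha, power, early stop and conclusion all rest on tumor control at the second CT scan, which is not a listed endpoint

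*Protocol article*

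**What the plan says.** **Named primary endpoint.** Study objectives states "The primary end-point of the study is progression-free survival (PFS") and defines it as a time-to-event measure, counted from the first infusion until progression is first documented. The Methods/Design part of the Abstract agrees: "The primary end-point of the study is progression-free survival". The secondary endpoints are overall survival, response rate, toxicity and the TIMP-1 biomarker work. Tumor control is in neither list.

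**Sample size and decision rule.** The Abstract says "A total of 25 evaluable patients (15 + 10 in two steps) will be included", under a Simon two-stage minimax design. The Statistics section sets the lower rate: "A tumor control rate less than 10 % after 4 months (at the time of the second evaluation CT scan) is not clinically relevant". With alpha 0.05 and power 80 %, the trial stops if none of the first 15 patients succeeds at the second scan. It continues to 25 if at least one does. If 5 of 25 succeed, "a tumor control rate of 30 % cannot be rejected, and it will be concluded that the treatment is effective enough to continue with future studies".

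**Planned analysis of PFS.** The Statistics section provides a Kaplan-Meier median and nothing further. As background it puts second-line PFS at around 4 months. The Discussion puts the median for the standard treatment at approximately 2 months, with 75 % progressed at 4 months.

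**Discussion.** The authors expect that 30 % "will have objective response after the first 4 months of treatment, thereby achieving an increased median PFS". They then describe the statistical basis of the protocol as a response rate of 30 % against the usual 10 %.

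**The concern.** The endpoint called primary is not the one that decides the trial. A reader of the Abstract or Study objectives expects a judgement on PFS time, with the quoted alpha and power behind it. The go/no-go rule counts a different quantity, and the Discussion names yet another as the basis of the design. Objective response and tumor control are not interchangeable here, because stable disease is a success under the Statistics section and a failure under objective response.

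Two things are at stake. First, the stated error rates do not apply to the named primary, for which no hypothesis exists. Second, the 10 % and 30 % rates were not clearly chosen for one outcome. In the Discussion 10 % is a response rate, while in Statistics it is the floor for tumor control. Which outcome is meant affects whether 10 % is a sensible null.

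**Working it through.** **Step 1. Which outcome does N = 25 belong to?**

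Inputs from the Statistics section: p0 = 0.10, p1 = 0.30, alpha = 0.05, power = 0.80, Simon minimax. Alpha is read as one-sided, as is usual for this design. With n1 patients in stage 1, n in total and n2 = n − n1, the trial stops if X1 ≤ r1 and succeeds if the total exceeds r:

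P(success | p) = Σ over x = r1+1 … n1 of b(x; n1, p) × P[Bin(n2, p) ≥ r + 1 − x]

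An exhaustive search for the smallest n with P(success | 0.10) ≤ 0.05 and P(success | 0.30) ≥ 0.80 returns n1 = 15, n = 25, r1 = 1, r = 5. That is the plan's 15 + 10. At one-sided alpha 0.025 the search returns n1 = 18, n = 29, so 25 fits only the one-sided 0.05 reading. The design is therefore built on a binary rate. No event count or power can be computed for PFS time, because the article gives it no null, target median or test.

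**Step 2. Do the stated alpha and power hold for tumor control as written?**

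| Rule | P(success) at 10 % (alpha) | P(success) at 30 % (power) |
|---|---|---|
| Minimax: stop at ≤ 1/15, success at ≥ 6/25 | 0.033 | 0.802 |
| As written: stop at 0/15, success at ≥ 5/25 | 0.098 | 0.909 |

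Five of 25 is read as five or more. The written numbers would arise if the largest failing counts (1 and 5) had been taken as the smallest passing counts. That is an inference; the article does not say so.

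**Step 3. The success outcome, sentence by sentence.**

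- Stage 1 stop: no patient with stable disease at the second scan.
- Continuation: one or more with partial response or stable disease.
- Final rule: tumor control after six courses.
- Complete response is not mentioned.
- Timing agrees: 2 × 9 weeks = 6 × 3 weeks = 18 weeks, which the article calls 4 months.

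**Step 4. The background PFS values against the 10 % null.**

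If PFS is exponential, the proportion progression-free at 4 months is 0.5^(4/median).

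- Median 2 months (Discussion): 0.5^2 = 0.25, which agrees with the Discussion's 75 % progressed.
- Median 4 months (Statistics): 0.5^1 = 0.50.

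Both lie above the 10 % floor for tumor control. If true tumor control were 25 %, the rule as written would declare success with probability 0.785, and the minimax boundaries with probability 0.616. This treats tumor control at the second scan as roughly the same as being progression-free at 4 months.

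**The case against.** The strongest defence is that the two quantities are close relatives. Missing scans and early stops aside, a patient with partial response or stable disease at the second scan is progression-free at that scan, so the decision outcome is nearly a landmark of PFS. The Statistics section introduces it directly after a PFS benchmark, and the Discussion argues from the proportion progressed at 4 months to a longer median PFS. Disease control also has a planned analysis, because the Statistics section names it among the quantities to be analysed. This makes the repair easy, but it does not remove the mismatch: the article never defines a PFS rate at the second scan, never calls it primary, and describes the design in the Discussion through objective response.

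A reader might infer that the trial could be declared positive on whichever measure looks best. The document does not support that. The Statistics section fixes a single go/no-go rule in advance, and neither PFS nor objective response has a success threshold. What remains is a risk of selective emphasis in reporting.

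A reader might also infer that PFS has no reference value at all. It has two, both background only; they disagree, and neither is tied to a test.

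Finally, 10 % may be meant as a floor of clinical relevance rather than as the result of standard treatment. The Statistics section does word it that way. The Discussion, however, presents 10 % as the usual response rate of second-line treatment, so the two uses still need to be reconciled.

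**Conclusion.** The point stands. PFS is the named primary, yet every design quantity and the conclusion ("it will be concluded that the treatment is effective enough to continue with future studies") rest on tumor control at the second CT scan, an outcome missing from the endpoint list. The stated alpha of 0.05 and power of 80 % do not apply to PFS. For tumor control under the written cut-offs, the values are 0.098 and 0.909.

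The mismatch itself is read directly from the text and needs no modelling. The error rates are exact binomial results that assume one-sided alpha and five or more successes out of 25. The comparison with 25 % additionally assumes that tumor control approximates freedom from progression at 4 months. This is an error in the plan as written, and a statistical analysis plan could not settle it without overriding one of these sections.

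**What to change.** 1. **Abstract and Study objectives:** name as primary the tumor control (progression-free) rate at the second CT scan, about week 18, which is the outcome the two-stage rule counts. Make PFS time secondary.
2. **Statistics, definition:** use one definition of success in the stage 1, continuation and final sentences, and say how complete response counts.
3. **Statistics, cut-offs:** either adopt the minimax boundaries (stop at ≤ 1/15, success at ≥ 6/25; alpha 0.033, power 0.802), or keep the written ones and restate alpha as 0.098 and power as 0.909. Renaming the endpoint alone would leave a primary whose stated alpha of 0.05 is not met.
4. **Discussion:** replace objective response and response rate with the chosen outcome wherever they carry the 30 % and 10 %. Reconcile the two PFS background values, and justify the 10 % null against the article's own 75 % progressed at 4 months.

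**Cost.** No extra data are needed, and N = 25 is unchanged as long as 10 % and 30 % are kept. If step 4 moves the null, N must be recalculated. PFS loses its headline status, and a running trial needs an endpoint amendment. Trial status reports 3 patients included, so the change can be made well before the stage 1 decision at 15.

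### The primary endpoint is labelled PFS, but its stated event leaves out death; it is therefore time to progression, and its Kaplan-Meier median would be biased upward

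*Protocol article*

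**What the plan says.** Under Study objectives, the article states: "The primary end-point of the study is progression-free survival (PFS"). It goes on to say that this endpoint is "defined as time from the first infusion of epirubicin to the first documented disease progression", judged by RECIST 1.1. Overall survival and toxicity are listed separately as secondary endpoints.

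Under Statistics, the analysis is given as follows: "PFS and OS will be calculated and reported as median survival (Kaplan-Meier method"). The same section cites a historical figure: "In randomized trials on second-line therapy, PFS is around 4 months". The Discussion cites another: "Median PFS of this standard treatment is approximately 2 months", and adds that "75 % of the patients will experience progressive disease after 4 months of treatment". It expects the trial to show a longer median PFS.

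The sample size and the decision rule under Statistics use a different variable: tumor control (partial response or stable disease) at the second CT scan, after six courses. Stage 1 accrual runs until 15 patients have either had that scan or progressed. Neither the endpoint definition nor this rule says what happens to a patient who dies first.

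**The concern.** As generally understood, PFS ends at progression or death, whichever comes first. An endpoint that ends only at documented progression is time to progression. Here the label and the definition disagree, and the definition is written out, so this is not a detail that the article leaves to a fuller document.

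The difference matters because the event needs imaging. A patient who deteriorates and dies between scans, or dies of toxicity, has no event. With a progression-only event, Kaplan-Meier treats that patient as censored, meaning as someone who might have progressed later at the same rate as those still followed. Patients who die early are unlikely to fit that description.

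Such deaths are plausible. Performance status 0 to 2 is admitted, eligibility asks for "a life expectancy of at least 3 months", and scans are 9 weeks apart. The second scan comes at about 6 × 3 = 18 weeks, beyond that minimum of roughly 13 weeks.

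What is at stake is the reported value of the declared primary endpoint. In a single-arm trial it can be set only against historical figures.

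**Working it through.** **Inputs from the article.** Event: documented progression only (Study objectives). Analysis: Kaplan-Meier median (Statistics). Historical medians: about 4 months (Statistics) and about 2 months (Discussion). Progressed by 4 months: 75%, leaving 25% (Discussion). Design: tumor control of 10% against 30%, with 15 + 10 = 25 patients. The error rates are stated as "Assuming a significance level at 0.05 (α = 0.05) and a power at 80 % (β = 0.20").

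**Input not in the article.** The share q of first events that are deaths without documented progression. It is assumed to be 10% to 20%, with 5% and 30% shown as outer values.

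**Step 1: the plan's own figures.**
- An exact search for the Simon minimax design with 10% against 30%, one-sided α 0.05 and power 0.80 gives 15 patients in stage 1 and 25 in total (stop at 1 or fewer of 15; not effective at 5 or fewer of 25). Exact α is 0.033 and power 0.802. The stated sample size reproduces, and no PFS quantity enters it. The decision boundaries printed in the article differ from these; that is a separate matter.
- With a constant hazard and a median of 2 months, the 4-month rate is 0.5^(4/2) = 0.25. The Discussion's two figures therefore agree with each other under constant hazards.

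**Step 2: effect of leaving out death.** With constant hazards, censoring the deaths removes a fraction q of the total hazard. Hence:
- median as reported = true median / (1 − q)
- 4-month rate as reported = (true 4-month rate)^(1 − q)

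| q | True median 2.0 reads | True median 4.0 reads | True 25% at 4 months reads |
|---|---|---|---|
| 5% | 2.11 | 4.21 | 26.8% |
| 10% | 2.22 | 4.44 | 28.7% |
| 15% | 2.35 | 4.71 | 30.8% |
| 20% | 2.50 | 5.00 | 33.0% |
| 30% | 2.86 | 5.71 | 37.9% |

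For example, at q = 20%: 2.0 / 0.80 = 2.50 months, and 0.25^0.80 = 0.330.

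**Step 3: check at the trial's size.** Simulated Kaplan-Meier medians with n = 25 and a true median of 4 months were 4.2, 4.5, 5.0 and 5.7 months for q = 5%, 10%, 20% and 30%. With death counted they were about 4.0 throughout.

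**Step 4: direction.** Dropping events from a Kaplan-Meier curve cannot lower it. The shift is zero only if nobody dies without documented progression.

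**The case against.** The strongest reply is that nothing in the plan's decision making uses this definition. The sample size, the interim stop and the final conclusion all rest on tumor control at the second scan. PFS is a descriptive median with no test or threshold. That is correct, and it limits the weight of the point.

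Several stronger readings are tempting, and the article does not support them.

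- A reader might infer from the 30.8% at q = 15% that a drug no better than standard would reach the plan's 30% target. It would not do so by this route. The 30% is a tumor control rate at the second scan, and censoring a death in the PFS curve cannot turn that patient into one with tumor control.
- A reader might infer that fatal toxicity is concealed. Overall survival and toxicity are separate secondary endpoints, so those deaths would be visible there.
- A reader might infer that early deaths are bound to be frequent. The life-expectancy criterion is a minimum, meant to screen out such patients, and the first scan falls inside it. Deaths before documented progression are plausible; their frequency is unknown.
- A reader might take it as shown that the historical figures are not comparable. Their definition of PFS is not given, and the Discussion's 4-month figure speaks of progressive disease.

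It is also fair that the shift is modest beside the precision available. With 25 events and an exponential median of 2.0 months, an approximate 95% interval is 2.0 × exp(±1.96/√25), or 1.4 to 3.0 months, against a shift of 0.2 to 0.5 months at q = 10% to 20%. But the shift is systematic, always in the favourable direction, and avoidable.

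**Conclusion.** The point stands as a correction to the endpoint definition. As written, the primary endpoint is time to progression under the name PFS, and its Kaplan-Meier median is biased upward whenever a patient dies without documented progression. At an assumed 10% to 20% of first events, a true 2.0 months reads 2.2 to 2.5 months, and a true 25% at 4 months reads 29% to 33%.

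These sizes rest on the assumed share, on constant hazards, and on such deaths being censored, which the stated event implies but the article does not spell out. The unfairness of the comparison with the historical medians further assumes that those count death. The Simon sample size and decision rule are not affected by the PFS definition. This should be fixed, but it does not undermine the design.

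**What to change.** Under Study objectives, define PFS as the time from first infusion to first documented RECIST 1.1 progression or death from any cause, whichever comes first. State that patients without either event are censored at their last adequate CT scan.

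For consistency, add under Statistics that a patient who dies before the second CT scan stays in the denominator and counts as not achieving tumor control. The stage 1 wording currently leaves such a patient in neither category.

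The cost is a few phrases. Dates of death are needed for overall survival anyway, no patients are added, and the total of 25 is unchanged. Reported PFS may be slightly less favourable. With only 3 patients on treatment according to Trial status, the change could be made well before any analysis.

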## Trial status

A total of 120 patients have been screened for *TOP2A* levels and we have found 14 patients (12 %) to have a *TOP2A*/CEN-17 ratio ≥ 1.5 in primary tumor, a metastatic lesion or both. To date 3 patients have been included and initiated treatment with epirubicin.

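### TIMP-1 cannot be validated as a marker of anthracycline sensitivity in a single-arm trial of at most 25 evaluable patients who all receive epirubicin; the objective should be worded as exploratory

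*Protocol article*

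**What the plan says.** The Design section fixes a single treatment group: "The study is an open label, single arm, phase II study". Under Treatment, epirubicin is the only study drug, and no comparator is described anywhere in the article. The Study objectives section then names, among the secondary end-points, "validation of tissue inhibitor of metalloproteinase-1 (TIMP-1) measured in plasma and immunohistochemically in tumor tissue, as biomarker for anthracycline sensitivity/resistance".

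The Statistics section derives the 25 evaluable patients (15 plus 10) from a Simon two-stage minimax design on tumor control. The uninteresting rate is 10%, the rate of interest is 30%, alpha is 0.05 and power is 80%. TIMP-1 plays no part in that calculation.

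The Design section describes the biomarker work more modestly: "A second aim is the collection of relevant tumor and blood material for subsequent biomarker studies".

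**The concern.** A marker of sensitivity or resistance to a drug class is meant to show who gains from that class and who does not. This is also how the Background section uses the idea, where predictive biomarkers are to guide the choice of drug. Showing it requires knowing how outcome varies with the marker under a different treatment, and this trial has no such patients. The word *validation* also implies an estimate firm enough to confirm the marker, which a sample chosen for another purpose may not give.

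At stake is what the trial may conclude. Its purpose is biomarker-guided treatment, so a TIMP-1 association presented as validation could be carried into later patient selection on evidence that does not support it.

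**Working it through.** **1. The plan's own sample size.** Inputs from the Statistics section: p0 = 0.10, p1 = 0.30, alpha 0.05, power 0.80. An exact binomial search for the minimax design returns 15 patients in stage 1 and 25 in total, with attained alpha 0.033 and power 0.802. The 15 + 10 = 25 therefore reproduces, on tumor control only. (The stopping and success limits written in the article are a separate matter and do not bear on this point.)

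**2. What the design can estimate.** Take two TIMP-1 groups, A and B, with tumor control rate p. The quantity that expresses sensitivity to the drug, as distinct from prognosis, is the interaction

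(p_A,epirubicin − p_B,epirubicin) − (p_A,other − p_B,other).

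The trial supplies the first bracket and has no data on the second. Suppose the first bracket is 45% − 15% = 30 percentage points (assumed rates).
- If the second bracket is also 30 points, the interaction is 0 and TIMP-1 is purely prognostic.
- If the second bracket is 0, the interaction is 30 points and TIMP-1 is predictive.

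The epirubicin data are identical in both cases. More patients in the same arm would sharpen the first bracket but never supply the second. The same holds for response, PFS and OS.

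**3. Precision with 25 patients.** At the hoped-for control rate, 0.30 × 25 = 7.5, so about 8 controlled and 17 not. Assume an observed AUC A = 0.70; the article gives no such figure. The Hanley-McNeil formula is

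SE² = [A(1 − A) + (n1 − 1)(Q1 − A²) + (n2 − 1)(Q2 − A²)] / (n1·n2),

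with n1 = 8, n2 = 17, Q1 = A/(2 − A) = 0.538 and Q2 = 2A²/(1 + A) = 0.576.
- Numerator: 0.210 + 7 × 0.0485 + 16 × 0.0865 = 1.933.
- SE = √(1.933/136) = 0.119.
- 95% CI: 0.70 ± 1.96 × 0.119 = 0.47 to 0.93.

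The interval includes 0.50, that is, no discrimination.

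**4. Power for a simple association.** All effects here are assumed. Splitting 25 patients 12/13 by TIMP-1, with overall control near 30%, the two-sided Fisher test at 0.05 gives:

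| Control rates by TIMP-1 group | Power |
|---|---|
| 45% vs 15% | 34% |
| 50% vs 10% | 58% |
| 55% vs 5% | 82% |

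For PFS with an even split and all 25 patients having an event, Schoenfeld's formula gives power Φ(½·√25·|ln HR| − 1.96). This is 41% at HR 0.50 and 63% at HR 0.40. Power of 80% would need 66 and 38 events respectively.

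**5. If the trial stops early.** Only 15 patients would be available. Under the written rule the trial stops when none of the 15 has tumor control, so there would be no controlled patients to compare on TIMP-1 at all.

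**The case against.** Several points can fairly be made for the plan.

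- The article does not use the word predictive for TIMP-1, sets no success criterion for it, and describes the biomarker aim as collecting material for later studies. A reader might infer that any TIMP-1 association would be reported as a validated predictive marker, but the document does not say so. What stands against the plan is the stated objective itself: *validation* is the article's own word, attached to sensitivity or resistance to the drug class.
- Imprecision is normal for a secondary biomarker analysis in a small phase II trial, no power is claimed for TIMP-1, and no AUC analysis is announced. This is fair, and it is why the figures above are illustrations only. It does not answer the missing comparator.
- A full protocol or analysis plan may hold more detail. It could specify cut-offs and tests, but no analysis of patients who all receive epirubicin can produce the missing contrast.

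Two stronger readings are tempting and should not be adopted.

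- It might be inferred that universal *TOP2A* amplification is what prevents validation of TIMP-1. Nothing in the article says that TIMP-1 fails to vary among amplified patients; the entry criterion limits only how far a result generalises.
- It might be inferred that the *TOP2A*–*TOP1* objective fails too, because enrolled patients all have a ratio of at least 1.5. The article says only "Additionally, the relationship between *TOP2A* and *TOP1* gene amplifications will be studied". It does not confine that work to enrolled patients and promises no conclusion. The Trial status section reports 120 screened patients, 14 of them amplified, so 120 − 14 = 106 below the threshold. A control arm is not needed for a tumor-to-tumor relationship, and the analysis population may be given in the full protocol.

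**Conclusion.** The point holds for TIMP-1 alone. The article states a secondary objective that its design cannot deliver: without patients on another treatment, prediction and prognosis cannot be separated at any sample size. That conclusion needs no numerical assumption.

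The second part, that at most 25 evaluable patients are too few to validate a marker, rests on assumed effects. An AUC of 0.70 would carry a 95% CI of about 0.47 to 0.93. Power for a tumor-control association would be 34% to 82% over the range tried, reaching 80% only for a gap as large as 55% versus 5%.

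TIMP-1 can still usefully be described against outcome, so the objective is over-worded rather than worthless. Severity is minor: the primary end-point, the stopping rule and the decision on further studies are unaffected.

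**What to change.** In the Study objectives section, replace the *validation* wording for TIMP-1 with *exploratory association of TIMP-1 (plasma and tumor tissue) with response, tumor control, PFS and OS under epirubicin*, reported with confidence intervals. Add one sentence stating that this single-arm trial cannot separate predictive from prognostic effects, and that no claim of validated or predictive anthracycline sensitivity will be drawn from it. This also brings the objective into line with the biomarker aim in the Design section.

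The cost is a weaker secondary biomarker claim. No extra patients, samples or assays are needed. No change to the *TOP2A*–*TOP1* objective is asked for.
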